### 2.3. Intervention

The TR group receives a personalized program for 8 weeks, including at least one session per day and is done through a web and mobile application. The telerehabilitation application allows health professionals to create personalized exercise programs, hold video conferences with patients, generate videos, images and parameters of each exercise, as well as send them by email and follow up patients through the mobile application.

The TR program describes the exercises to be performed, the number of series and repetitions, and the criteria for progression, which will be based on the clinical guidelines published for patients with COVID-19 and described in the introduction section. The Physiotec software was selected by the research team to be best suited to the needs of the patients.

Patients are initially supervised by the research team who will conduct training sessions to ensure proper execution of the exercises and encourage patient adherence. Patients will be instructed to perform self-training by following the video exercises through the TR program, as well as a support document called COVID-19 Patient Telerehabilitation Manual. The number of synchronous sessions (1 to 1) via videoconference will be determined by the initial evaluation, limiting the interventions to 1 session per day of maximum 45–50 min, always adapted to the previous evaluation and to the needs of each patient.

Patients will be advised to refrain from any other specific training during the intervention period. Any deviation from the adherence and practice of the TR program is recorded on a daily basis, noting any adverse incidents.

Telerehabilitation and physical therapy interventions may include aerobic training—generate exercise patterns such as walking, fast walking, jogging, swimming, etc., starting at a low intensity and duration and increasing gradually; 20–30 min of session duration is recommended, 3–5 sessions/week, although it will always depend on the sensation of fatigue and/or dyspnea that each patient presents [18]. Progressive strength training is recommended working 1–3 muscle groups with a load of 8–12 repetitions, with 2-min training intervals. The frequency would be 2–3 sessions/week for a minimum period of 6 weeks, increasing the load by 5–10%/week [18]. Secretion drainage or ventilatory techniques to re-educate the respiratory pattern, improve ventilation, mobilize the thorax and favor secretion drainage, especially in those patients with chronic pathology prior to COVID-19 or who have a reduced pulmonary capacity to cause the disease [36].

Due to the lack of detailed knowledge of sequelae, a correct evaluation of each particular case is recommended before applying physiotherapeutic techniques [16]. The software and the mobile application for such intervention are provided and financed by exclusive license by the principal researcher. Customized exercise program examples are available at main author request.

The control group (CG) receives the standard of care recommended for patients discharged from hospital. Based on the individual needs of each subject, it consists of a rehabilitation program in their hospital or primary care center of reference, in the event that they present evidence of immunity and the evaluation of the sequelae requires it. If you do not present proof of immunity or if you test positive for COVID-19, you will receive a recommendation for confinement for a minimum of 14 days and a health education program to be carried out at home where recommendations for the care of health sequelae are included.

### 2.4. Outcome Measures

The initial assessment includes a self-made clinical interview for anamnesis conducted via videoconference.

#### 2.4.1. Affiliation Data and Socio-Demographic Questionnaire

Including age, gender, location and other socio-demographic variables.

#### 2.4.2. Main Explanatory Variable

##### Functional Capacity: For the Evaluation of the Functional Capacity and Fragility of the Patients the Following Tests Will Be Performed

Firstly, the “sit-to-stand test in 1 min” (1-min sit-to-stand, STS). This assessment of functional capacity in patients with respiratory impairment is an excellent alternative to the 6-min walk test (6MWT) which has certain limitations with regard to the space requirements for its execution. The 1-min STS test is a reliable, valid, and responsive test for measuring functional exercise capacity in patients with airway impairment and elicited a physiological response comparable to that of the 6MWT [37]. To carry out this test, the standardized protocol described by Crook and collaborators [37] will be used.

Secondly, the short performance physical battery test (SPPB). This is a widely used and validated test battery with high internal consistency, which evaluates three points: walking speed with the 4-m walk test; strength and resistance of the lower limbs by counting the time required to perform 5 squats (sit-to-stand test), and balance by standing with feet together, in tandem and semi-tandem. Each item is evaluated with a score from 0 to 4. The maximum final score is 12. An outline and protocol of the test execution is presented at Figure 2 [35].

##### Quality of Life

The SF-12 and EuroQoL-5d questionnaires will be used for the assessment of health-related quality of life.

The SF-12 questionnaire is the short version of the SF-36, presenting good correlation and being considered an adequate instrument of choice to measure the general health status of the population [38]. The SF-12 questionnaire assesses eight dimensions of health-related quality of life: physical function, physical role, body pain, general health, vitality, social function, emotional role and mental health [39]. The EuroQoL-5D assessment questionnaire (EQ-5D) contains a descriptive system of one’s health status measured in five dimensions (mobility, self-care, activities of daily living, pain and anxiety/depression). The EQ-5D has a visual analogue scale (VAS) that assesses the state of health “today” with scores ranging from 0 (worst imaginable health) to 100 (best imaginable health). With the EQ-5D questionnaire, information is obtained on the level of the problem (no problem, some/moderate problem or severe problem [39].

#### 2.4.3. Secondary Explanatory Variable 

##### Satisfaction and Usability

The acceptance and usability of telemedicine applications is a prerequisite for identifying the potential clinical benefits of this technology. It is therefore important to complement this research with tools that examine patient satisfaction and perception [40]. An adaptation of the Telemedicine Satisfaction and Usefulness Questionnaire (TSUQ), whose psychometric analysis supports construct validity and internal consistency reliability and which is available in English and Spanish will be used [40]. The instrument used showed high reliability (Cronbach’s alpha 0.8) and evidence of validity with respect to perception in telemedicine [41]. Includes 17 questions that are assessed with a 5-point Likert subjective scale (1 totally disagree and 5 completely agree). The individual obtains scores from 17 to 85. The higher the score, the better the perception of the telerehabilitation intervention. Therefore each of the scores of the 17 variables indicated and finally the total score of the Test will be analyzed [40,41].

##### Analysis of the Cost-Effectiveness

To assess the cost-effectiveness of the telerehabilitation intervention, the international guidelines for conducting cost analyses in randomized clinical trials will be followed [42]. Such an economic analysis is based on the health sector perspective, which means that only costs corresponding to health interventions will be considered, and not related costs to the patient. Therefore, only costs related to the provision of health services will be taken into account [43].

Costs are divided into two categories of variables: firstly, costs related to clinical aspects (direct costs) and secondly, costs related to the use of the technology (indirect costs).

Direct Costs: Numerical variable calculated on the basis of the number of hours of intervention and the cost of the Physiotherapist according to the hourly wage in force in the health system in the centers where the research is carried out. It will be calculated based on the recording of the number of sessions in both groups.

Indirect Costs: Numerical variable calculated based on the cost of using the technology for the telerehabilitation platform.

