## 1. Introduction

Severe acute respiratory syndrome coronavirus 2 (SARS-CoV-2) causes coronavirus disease 2019 (COVID-19). On 11 March 2020, COVID-19 was categorized as a pandemic and its outbreak was declared a public health emergency of international concern [1,2,3]. Current reports estimate that 80% of cases are asymptomatic or mild; 15% of cases are severe (infection requiring oxygen supply); and 5% are critical patients requiring ventilation and life support [2,4,5,6]. The average time from symptom onset to recovery is two weeks when the illness is mild; and three to six weeks when it is severe or critical. It should be noted that between 75–80% of hospitalized patients will be admitted to hospital for a long period of time (±21 days) [7].

COVID-19 can cause important sequelae in the patient after the virus has been overcome, one of the main ones being respiratory system involvement by bilateral pneumonia. Loss of strength, dyspnea, polyneuropathy and multiorgan involvement (liver, myocarditis and even brain damage) are also common [5,8,9]. Consequently, physiotherapy is playing a vital role in this pandemic and will be fundamental in improving the health of many of the patients. Recent studies already indicated a loss of pulmonary capacity of between 20% and 30% [10]. Therefore, it is a multiorgan disease with a wide and heterogeneous range of sequelae, the extent of which is not yet known [11].

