The main objective of this research is to evaluate the effectiveness of a personalized telerehabilitation intervention in patients diagnosed with COVID-19 after discharge from hospital for the improvement of functional capacity and quality of life compared to a program of health education and/or care in a rehabilitation center. As secondary objectives, to identify the satisfaction and perception of patients with the telerehabilitation intervention and the presence of barriers to its implementation, as well as to evaluate the cost-effectiveness from the perspective of the health system. The hypothesis of this research is that the implementation of a telerehabilitation (TR) program in patients with COVID-19 presents no inferior results in the improvement of functional capacity and quality of life compared to those obtained with a health education program and/or care in a rehabilitation center.

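### The economic objective takes the health-system perspective, but the cost definition names only physiotherapist hours and platform use, so as written it compares programme delivery costs

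*Protocol article*

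**What the plan says.** The Abstract and the objectives at the end of section 1.2 of the Protocol article list, among the secondary objectives, the aim "to evaluate the cost-effectiveness from the perspective of the health system".

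Section 2.4.3, Analysis of the Cost-Effectiveness, repeats the perspective ("Such an economic analysis is based on the health sector perspective"), leaves out patient-borne costs, and states the scope: "only costs related to the provision of health services will be taken into account". The section continues "Costs are divided into two categories of variables" and defines each:

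- Direct cost is a "Numerical variable calculated on the basis of the number of hours of intervention and the cost of the Physiotherapist according to the hourly wage", to be worked out from the sessions recorded in each arm.
- Indirect cost is the cost of using the telerehabilitation platform.

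The section also says that international guidance on cost analysis in randomised trials will be followed, but it names no further resource item. Table 1 has one cost row, for direct costs, marked at week 4, week 8 and close-out. It has no row for health-service use.

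The patients have recently left hospital, and section 2.1 includes those with severe or critical disease. Of COVID-19, the Introduction says that "it is a multiorgan disease with a wide and heterogeneous range of sequelae, the extent of which is not yet known". The Conclusions expect the identified resources and costs to help shape new intervention policies.

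**The concern.** A health system that pays for rehabilitation also pays when the same patient is readmitted, attends an emergency department or makes an unplanned visit to primary care or a specialist. In patients discharged after COVID-19, such use within 8 weeks is plausible. It could differ between remote care and the control pathway in either direction: closer contact might prevent some of it, or might prompt more referrals. A cost definition limited to session hours and platform use cannot show either effect.

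At stake is what the economic result means. Counted cost would mostly reflect how intensively each programme is delivered. Section 2.3 already makes that differ by arm. The telerehabilitation group has a daily programme with videoconference sessions as needed. Some control patients may have few or no physiotherapist sessions, because those without proof of immunity receive confinement advice and home education. A reader of the final report who sees a health-system perspective would expect downstream care to have been counted.

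**Working it through.** The article states no cost, rate or incremental ratio, so there is no figure to reproduce. The check has two parts.

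**1. Stated scope against listed items (section 2.4.3 and Table 1)**

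- Who bears the cost: the health sector; patient costs are out.
- What is in scope: the cost of providing health services.
- What is listed: two categories, each defined. One is intervention hours times wage; the other is platform use.
- Where other care would fall: a readmission or emergency visit is neither an intervention hour of a physiotherapist nor platform use, so it fits neither category.
- Whether another data source fills the gap: the adverse events named in the Discussion are lack of improvement, low adherence and muscle overload from excessive workload. Section 2.3 has adverse incidents noted alongside adherence to the telerehabilitation programme. Neither is linked to costs or described as a count of service use in both arms.
- What is already counted: control-arm rehabilitation at a hospital or primary care centre enters through the session records. The gap is therefore care outside the trial interventions.

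**2. Possible scale (illustration; every unit cost, risk and wage is an assumption)**

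Shift in mean cost difference per patient = cost per readmission × between-arm difference in readmission risk.

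- Low end: EUR 2,000 × 0.02 = EUR 40
- Middle: EUR 4,000 × 0.05 = EUR 200
- High end: EUR 8,000 × 0.10 = EUR 800

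As a yardstick, physiotherapist cost per telerehabilitation patient = hours × wage, with the wage assumed at EUR 15 to 40 per hour.

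- Ceiling from section 2.3 (one session a day, 50 minutes, 8 weeks): 56 × 50 / 60 = 46.7 h, or EUR 700 to 1,867.
- Assumed lighter course: 12 × 45 / 60 = 9 h, or EUR 135 to 360.

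On these ranges the omitted item runs from small beside the counted cost to larger than the counted cost of a light course. The proper comparator is the between-arm difference in delivery cost, which the article does not give.

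**Precision.** With an assumed 5% readmission risk and 118 patients per arm (section 2.1 gives 118 and 117), the standard error of the risk difference is √(2 × 0.05 × 0.95 / 118) = 0.028, or 2.8 percentage points. At EUR 3,000 to 6,000 per readmission that is about EUR 85 to 170 per patient. A true difference of 3 points would be worth 0.03 × 3,000 = EUR 90 to 0.03 × 6,000 = EUR 180, about the same as the noise.

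**The case against.** The strongest reply is that the section sets its own scope. Besides the sentence on provision of health services, it says that only the costs of health interventions will be considered. Both sentences restrict; neither promises every service a patient uses. Costing the two compared interventions as the provider bears them fits that wording. This stands to the extent that the perspective alone does not prove a contradiction. But if that is the intended reading, the result is a delivery-cost comparison, and the objective should be labelled so.

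A second reply is that this is a condensed article, and a resource-use form may sit in the full protocol. Table 1 is also visibly incomplete: it has no row for indirect costs, although the text defines them. A reader might infer that no other care use is recorded in either arm and that it can never enter the result. The documents do not support that. They show only that the cost definition does not name such care and that the schedule shows no item for it. The point survives because the article does more than omit detail: it fixes a two-item cost rule narrower than the objective it serves.

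Third, the money figures above rest on assumptions, and a readmission difference of the size illustrated is close to chance variation in this trial. That stands. It limits what the added data could show, but does not make the two-item rule match the objective.

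**Conclusion.** The point holds as a mismatch between label and content. Applied as written, the cost rule gives a comparison of programme delivery costs, while the objective announces cost-effectiveness for the health system. The size and direction of any resulting bias cannot be derived from the documents. The illustrative EUR 40 to 800 per patient rests wholly on assumed readmission costs and risk differences.

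A reader might go further and infer that telerehabilitation will wrongly be declared cheaper, or that the sign of the cost difference would reverse. The documents support neither: they contain no cost data and no decision rule. The Conclusions present the costs as informing policy, which is weaker than setting it.

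This is one secondary objective. The functional-capacity and quality-of-life comparisons are unaffected. The change is a cheap improvement and does not bear on the trial's main result.

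**What to change.** Either of two changes would bring objective and cost rule into line.

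1. **Preferred: measure the missing item.** At the existing week-4 and week-8 assessments, ask both arms for a short count of health-service use since the previous assessment: readmission days, emergency attendances, and unplanned primary-care and specialist visits. Restrict it to care outside the trial interventions and exclude rehabilitation sessions already costed. Without that rule, control-arm sessions at hospitals and primary care centres would be counted twice. Cost the items at health-system tariffs, add them to direct cost, and report the incremental cost with and without them. Collect the data prospectively, or link to health records before the anonymisation described in section 2.5, because a later look-up may be impossible once the link to the person is removed.

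2. **Otherwise: relabel.** Keep the payer perspective, which correctly says whose costs count, but describe the objective and conclusion as a comparison of intervention delivery costs that excludes downstream care.

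The first option costs a few questions at visits already planned, plus tariff work. It also makes the incremental cost less precise, since readmissions are likely to be few at about 118 per arm; reporting both versions makes that visible. The second option costs only a change of wording.

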Unlike other studies that require software implementations in specific devices, our intervention generates few obstacles since it is available in any device that allows internet connection and that patients usually have (personal computer, laptop, tablet, smartphone) allowing access from any location and different devices. This contrasts with other studies that require a highly complex technological platform, software installation and multidirectional cameras for controlled clinical control connecting the healthcare provider and the patient [47]. As the patient uses his own technological devices, the rapid implementation process is guaranteed. This, however, may lead to a selection bias for those patients without access to technology. Technical problems (disconnection, device failures) and technological difficulties may arise in connection with the use of technology. However, staff members will be available to provide technical support to patients by phone or email, without the need to visit the patient at home to install or check any hardware.

The lack of improvement and positive evolution of the patient, as well as the appearance of a low level of adherence was considered as possible adverse events. Also is considered as an adverse event, the performance of movements with excessive workload that cause muscle overload.

Patients will be informed of the importance of warning the healthcare professional of any incident or setback in their recovery, as well as their right to withdraw from participation in the research at any time.

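### A session count does not measure therapist hours in the telerehabilitation arm, and the two cost categories leave some staff time and the licence price open, so incremental cost may be biased in either direction

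*Protocol article*

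**What the plan says.** The protocol article, section 2.4.3 (Analysis of the Cost-Effectiveness), takes a health-sector perspective, under which "only costs related to the provision of health services will be taken into account". It names two categories.

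- **Direct cost** is "calculated on the basis of the number of hours of intervention and the cost of the Physiotherapist according to the hourly wage in force", and on the quantity to be recorded: "It will be calculated based on the recording of the number of sessions in both groups".
- **Indirect cost** is "Numerical variable calculated based on the cost of using the technology for the telerehabilitation platform".

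Section 2.3 describes the telerehabilitation (TR) arm as an 8-week programme with one or more sessions every day through a web and mobile application. Within it, "Patients will be instructed to perform self-training by following the video exercises through the TR program". The number of live one-to-one videoconferences is set for each patient from the initial evaluation. Interventions are capped at one session a day of at most 45–50 minutes. The research team also gives initial training sessions, and the application is used to build individual programmes and follow patients up. The software is "provided and financed by exclusive license by the principal researcher". The Discussion adds that "staff members will be available to provide technical support to patients by phone or email".

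Cost-effectiveness from the health-system perspective is a stated secondary objective (Introduction). The Conclusions expect the allocated costs to inform new policies.

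**The concern.** The rule turns a number of sessions into wage hours. That works where every recorded session has a therapist present. In the TR arm the same word covers both live contact and the daily programme, part of which the patient does alone from videos. If the recorded count covers the daily programme, time with no therapist present is priced at the wage and TR looks dearer than it is.

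The other gaps act the opposite way. Staff work outside a session has no line to be entered on, and a licence that someone other than the health system pays for could be entered at a nil price. Both would make TR look cheaper than it would be in routine use.

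At stake are the size of the incremental cost and, in some scenarios, its sign. If only session counts are kept, live time and self-training may not be separable afterwards.

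**Working it through.** The article gives no wage, session total or cost result, so there is no figure to reproduce. What follows is a sensitivity calculation.

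**Inputs from section 2.3:** 8 weeks; at least one session a day; at most 45–50 minutes per session; number of live sessions not fixed.

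**Assumptions:** *s* live sessions per week, with *s* from 1 to 7; live and self-training sessions of equal length; the stated maximum used as the length.

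**Step 1. All daily sessions counted.** Sessions = 8 × 7 = 56. Hours = 56 × 45/60 = 42.0 to 56 × 50/60 = 46.7 per patient.

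**Step 2. Live sessions only.** Hours = 8 × *s* × minutes/60. Overcount = 56/(8*s*) = 7/*s*.

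| Live sessions per week (assumed) | Hours at 45 min | Hours at 50 min | Overcount |
|---|---|---|---|
| 1 | 6.0 | 6.7 | 7.0 |
| 2 | 12.0 | 13.3 | 3.5 |
| 3 | 18.0 | 20.0 | 2.3 |
| 5 | 30.0 | 33.3 | 1.4 |
| 7 | 42.0 | 46.7 | 1.0 |

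With equal lengths the ratio does not depend on the minutes chosen. The hours do, and they would be lower for sessions shorter than the maximum.

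**Step 3. Effect on the difference between arms.** Let the control arm have *c* therapist sessions per week. The article gives no number, so *c* is an assumption. At 45 minutes each:

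- all TR sessions counted: 8 × (7 − *c*) × 45/60
- live TR sessions only: 8 × (*s* − *c*) × 45/60

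With *c* = 3 and *s* = 2, the first gives 8 × 4 × 0.75 = +24 hours for TR and the second 8 × (−1) × 0.75 = −6 hours. The sign changes whenever *s* < *c* < 7. It does not change if control patients have no therapist sessions: with *c* = 0 and *s* = 2 the results are +42 and +12 hours.

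**Step 4. Items against categories.**

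| TR item | Place in the article | Cost category |
|---|---|---|
| Live one-to-one sessions | 2.3 | Direct |
| Self-training sessions | 2.3 | Direct if the count covers the daily programme; not stated |
| Initial training sessions | 2.3 | May be among the recorded sessions; not stated |
| Programme building and follow-up through the app | 2.3 | Neither: not a session, not platform use |
| Technical support by phone or email | 3. Discussion | Neither |
| Platform licence | 2.3 | Indirect; basis of valuation not stated |

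**The case against.** The strongest reply is that a rule built on hours of intervention and a physiotherapist's wage most naturally means hours that a physiotherapist delivered. The article nowhere says that self-training is charged at the wage. This stands: a reader might infer that unsupervised exercise is priced as therapist time, but the text does not say so. It leaves the costed session undefined. The reply does not remove the difficulty, because the stated quantity is a number of sessions, and section 2.3 uses that word in both senses.

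Second, the share of live contact is unknown. Section 2.3 does not say that TR is mostly self-training, and with a live session every day the overcount is nil. This also stands, and it is why the size is given as a range.

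Third, a reader might infer that the licence and the initial training are left out. The documents do not support that. The platform has its own cost line, with only its valuation open, and training sessions may be within the count. The absence of a technology row in Table 1 proves little, since a platform price is not a visit assessment. Whether to add centre overheads in the control arm is a costing preference, not an error.

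Fourth, an article leaves unit prices and logging forms to a fuller document, and this one says that it will follow international guidelines for cost analyses in trials. That is fair for those details. It does not cover the point here, because the article itself fixes the quantity to be recorded and the two categories.

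**Conclusion.** The point holds as a defect in a stated costing rule. Recorded sessions do not measure therapist hours in the TR arm unless live sessions are separated from the daily programme. Technical support and asynchronous programme work fall outside both categories. The self-financed licence has no stated price basis, so a nil price is possible.

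The gap in TR therapist time is 42.0–46.7 hours against 6.0–20.0 hours per patient for an assumed one to three live sessions a week, at the maximum length. That is an overcount of 7.0-fold to 2.3-fold, falling to 1.0 if every daily session is live. The change of sign in Step 3 rests on assumed frequencies in both arms.

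It would be tempting to conclude that the cost-effectiveness result will be wrong. The documents do not support that: no unit cost, control session number or result is given, and the errors partly offset each other. What can be said is that the incremental cost may be biased in either direction, by an amount that the article does not allow one to fix. The article should be changed on this point, since the objective is a stated one and the missing data may not be recoverable later.

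**What to change.** In section 2.4.3, replace the number of sessions with logged staff minutes in both arms, multiplied by the relevant hourly wage. For TR, log live sessions, initial training, programme preparation, follow-up through the app and technical support. Self-training with no staff present counts as zero. For control, log the staff minutes of the sessions delivered.

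For the platform line, state that it is valued at the price per patient that the health system would pay, whoever financed the licence in the trial.

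The cost is a short time log in both arms and a price quotation for the licence. The downside is a small recording burden and possibly a less favourable cost for TR once support time and the licence are fully counted.
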